#### Statistical Considerations Regarding the Design

The primary statistical analysis will use an intention-to-treat approach. Therefore, all patients involved in the study will be included in the final analysis. Results will be presented using descriptive statistics (mean, SD, median, and range for continuous variables and proportions for nominal variables). Patient baseline characteristics will be compared using a 2-sample *t* test or a nonparametric test for continuous variables, and the Pearson chi-square test will be used for qualitative variables. All statistical analyses will be conducted using 2-tailed tests and adopting a 5% significance level. The effect of the interventions on the primary end point will be analyzed using the Cox proportional hazards model. Point estimates and 95% CIs will be calculated for the hazard ratio of the standard practice group versus the enhanced behavioral and psychological monitoring group. Any statistically significant difference between the 2 groups at baseline will be balanced by the multivariable adjustment. A logistic regression or Cox proportional hazards model will also be used to evaluate the effect of the interventions on the secondary end points in the 2 groups. Continuous variables such as those obtained from imaging and biochemical and molecular biomarkers will be summarized descriptively at baseline and follow-up visits. The differences between the 2 groups during the different follow-up visits will be evaluated using the analysis of covariance considering the corresponding baseline measurement as a covariant.

Finally, for the cost-effectiveness analysis, the health and QoL outcomes observed during the study will be used to calculate the QALYs. These QALYs will be combined with cost data in a cost-utility analysis to estimate the cost per QALYs associated with the implementation of the CARDIOCARE model and the eHealtHeart interventions. The incremental cost-effectiveness ratio will also be calculated to evaluate the CARDIOCARE model’s effectiveness compared to current care practices. Therefore, the incremental cost-effectiveness ratio, which will be calculated using a threshold approach, will allow us to better understand how to distribute and allocate the different health care resources.

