### Study Design

This multicenter clinical study has been designed as a prospective observational study that examines whether integrated patient-oriented psychological, behavioral, and functional interventions can prevent, delay, or mitigate cardiotoxicity as an adverse effect of cancer therapy. It will include 750 older patients with breast cancer recruited across the participating clinical centers.

All recruited patients will be randomly assigned to either the standard practice or enhanced monitoring group. Patients in both arms, in addition to standard oncological care, will receive eHealth monitoring through the Garmin Venu SQ and Polar H10 technologically advanced wearable devices (described in detail in the Instruments and Measures section) and will have access to the ePsycHeart assessment tool on the CARDIOCARE mobile app (described in detail in the Instruments and Measures section). Furthermore, patients will be given a Motorola smartphone on which the CARDIOCARE mobile app is installed. These technological instruments will provide clinicians with the patients’ physical and psychological intrinsic capacity and QoL indicators as foreseen in the study protocol. However, only patients in the intervention arm will have access to the behavioral, psychological, functional, and educational interventions in the eHealtHeart section of the CARDIOCARE mobile app, which will allow researchers to evaluate the effectiveness of such eHealth interventions on the intrinsic capacity and QoL of older patients with breast cancer, as well as these interventions’ effectiveness in mitigating, delaying, or even preventing the onset of cardiac toxicity associated with breast cancer treatments.

As per the protocol, before undertaking any study procedure, the patients will receive a patient information sheet, in which the different study procedures are explained in lay language. The same document also sets out the study’s risks, benefits, and aims. Once the patient has read the patient information sheet and has received answers to any questions or concerns, she can choose to provide informed consent to participate in the study by signing the written informed consent form, of which she will be left with a copy, whereas the CARDIOCARE researchers will keep the original document.

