Patients will be assigned through the study electronic case report form (eCRF) at baseline to the standard practice or enhanced monitoring group in a 1:1 ratio. The study time points, follow-ups, and specific procedures are detailed in the Study Time Points and Procedures section (Figure 1).

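### The primary Cox model takes its covariates from baseline significance tests between randomised arms, so chance chooses the model and prognostic factors are usually left out

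*Protocol article*

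**What the plan says.** Study Design states that "All recruited patients will be randomly assigned to either the standard practice or enhanced monitoring group" and gives the allocation as "standard practice or enhanced monitoring group in a 1:1 ratio". The same section also says the study "has been designed as a prospective observational study".

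Statistical Considerations Regarding the Design sets out the analysis:

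- Baseline: "Patient baseline characteristics will be compared using a 2-sample" *t* test or a nonparametric alternative, with chi-square tests for categorical variables.
- Threshold: "All statistical analyses will be conducted using 2-tailed tests and adopting a 5% significance level".
- Primary analysis: "The effect of the interventions on the primary end point will be analyzed using the Cox proportional hazards model", reported as a hazard ratio between the arms.
- Covariates: "Any statistically significant difference between the 2 groups at baseline will be balanced by the multivariable adjustment". This sentence follows the primary Cox model and comes just before the logistic and Cox models for the secondary end points. Neither set of models has a covariate named in advance.
- Continuous imaging and biomarker measures: "The differences between the 2 groups during the different follow-up visits will be evaluated using the analysis of covariance", with the matching baseline value as covariate.

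Potential Limitations adds that differences between populations, cultures and environments will be taken into account in the analysis plan. It names no variable and no model.

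**The concern.** When allocation is random, a test of baseline difference addresses a null hypothesis already known to be true. A small p value shows that chance produced an imbalance. It does not show whether the variable is related to cardiotoxicity. What makes a covariate worth including is its relation to the outcome, and the rule never looks at that.

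Two consequences follow. First, nobody can say what the primary model is until the baseline table has been run. Second, a strong predictor enters only if it happens to be imbalanced, while an irrelevant variable enters on the same terms.

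This matters in CARDIOCARE because the Inclusion Criteria run from adjuvant endocrine therapy to anthracyclines, anti-HER2 therapy and first-line metastatic treatment. The article itself says that different treatments cause different types of cardiotoxicity. One of its aims is to predict cardiotoxicity from baseline data, yet the between-arm comparison is not set up to use such predictors. What is at stake is the power of a trial planned at 80% and the credibility of its primary hazard ratio.

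**Working it through.** **1. The plan's own figure.** Sample Size Considerations gives 21% incidence, a 40% relative reduction (0.21 × 0.6 = 12.6%), two-sided alpha 0.05, power 0.80, 10% dropout and Fisher's exact test. Exact power is 0.801 at 331 per arm. Then 331 / 0.9 = 367.8, rounded up to 368 per arm, or 736 in total. The stated 736 is reproduced and is not in dispute.

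**2. How often the rule selects anything.** Each baseline test has a 5% chance of significance under randomisation. With *k* independent variables, P(at least one selected) = 1 − 0.95^*k*. The article does not list the variables to be tested, so *k* is an assumption:

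| *k* | Expected number selected (0.05*k*) | P(at least one) |
|---|---|---|
| 5 | 0.25 | 22.6% |
| 10 | 0.5 | 40.1% |
| 20 | 1.0 | 64.2% |
| 30 | 1.5 | 78.5% |

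Correlated variables, such as related echocardiographic measures, would change these figures.

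**3. How often it selects something useful.** A given prognostic factor is included with probability 0.05 and left out with probability 0.95. With two such factors, P(at least one included) = 1 − 0.95² = 9.75%.

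**4. Effect on power.** Simulated Cox analyses used 736 patients, 12 months, hazard ratio 0.6, control risk about 21%, 10% early censoring, and 10 independent baseline variables of which two are prognostic. There were 2,000 trials per row. The prognostic strengths are assumptions.

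| HR per SD of each factor | Unadjusted | Significance rule | Two factors fixed in advance | Gain over rule |
|---|---|---|---|---|
| 1.35 | 0.7700 | 0.7695 | 0.7810 | 1.2 points |
| 1.65 | 0.7370 | 0.7355 | 0.7790 | 4.4 points |
| 2.0 | 0.6755 | 0.6815 | 0.7705 | 8.9 points |

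The Monte Carlo standard error of one entry is about √(0.77 × 0.23 / 2000) = 0.009, so the rule cannot be told apart from no adjustment, and the gain in the first row is small. The columns should be compared within a row. The levels depend on the simulation set-up and do not re-estimate the planned 80%. Some variable was selected in about 40% of these trials, but a prognostic one in only about 9–10%, in line with steps 2 and 3.

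**5. Effect on type I error.** With hazard ratio 1 and 4,000 trials per row (Monte Carlo standard error about 0.0035):

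| HR per SD | Unadjusted | Significance rule | Fixed in advance |
|---|---|---|---|
| 1.35 | 0.0595 | 0.0585 | 0.0578 |
| 1.65 | 0.0518 | 0.0522 | 0.0538 |
| 2.0 | 0.0498 | 0.0468 | 0.0468 |

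The rule shows no inflation relative to the other two analyses.

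**6. Room for covariates.** At the planning rates, the 331 per arm retained give 331 × (0.21 + 0.126) = 111 events. Arm, age, troponin I, LVEF and four treatment indicators are 8 coefficients, or 111 / 8 ≈ 14 events each. Stratifying by centre adds no coefficient. A short list is affordable.

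**The case against.** **The primary test stays valid.** This stands. A reader might infer that the rule inflates the false-positive rate. Among trials whose imbalance in a strong predictor is moderate but not significant (1 to 1.96 standard errors), the unadjusted test does reject too often: 5.2%, 5.7% and 7.4% in a logistic simulation with log-odds 0.7, 1.0 and 1.3 per SD. Trials with imbalance of 1 standard error or less offset this (4.2%, 4.1% and 3.5%), and overall error under the rule was 4.5–4.7%. The stratum figure alone would mislead.

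**The loss is not one of precision.** This also stands. In Cox and logistic models, adjustment for a prognostic factor moves the treatment estimate away from the null and does not shrink its standard error. In the logistic simulation the standard error rose from 0.192 to 0.199–0.215. The loss is in power, and its size rests on prognostic strengths the article does not give.

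**The article does not say that nothing else will be adjusted for.** This is true, so the documents do not establish that centre, for example, will be ignored. Potential Limitations points to an analysis plan that is not shown, and a full covariate list could sit there. But that sentence names no covariate or model and does not withdraw the rule. The point rests on the rule as stated, not on a missing list.

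**The study is labelled observational.** The same section assigns patients at random, and the analysis is by intention to treat. Even in an observational comparison, significance is a poor way to choose confounders.

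**Conclusion.** The point holds as a badly fixed rule for the Cox and logistic comparisons. The primary model depends on the data, and any given prognostic factor is left out about 95% of the time. The analysis of covariance of continuous markers lies outside the rule and is sound in this respect.

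The power forgone is about 1 to 9 points over the assumed range of prognostic strength, with two prognostic factors among 10 independent variables. The chance that something is selected at all is 40% with 10 independent variables and 64% with 20. A larger assumed number would raise that chance, but the article gives no number to support one.

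The documents do not support a claim that the primary result would be invalid. The analysis under the rule does about as well as an unadjusted one, which is legitimate in a randomised trial. This should be fixed because the remedy is cheap and better, not because the trial fails without it.

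**What to change.** Delete the significance-based rule and do not use baseline tests to select covariates. Baseline characteristics can be described by arm without p values.

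Before outcome data are compared by arm, name a short covariate set for the primary Cox model and use it whatever balance is observed. For example:

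> *The primary Cox model is stratified by centre and adjusted for age, baseline troponin I, baseline LVEF and planned systemic treatment at baseline, entered as separate indicators for anthracycline, taxane, anti-HER2 and endocrine therapy. The unadjusted hazard ratio is reported alongside.*

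The treatment indicators must not be mutually exclusive classes, because the Inclusion Criteria allow anti-HER2 therapy with chemotherapy. The report should note that adjusted and unadjusted hazard ratios are different estimands, so some difference between them is expected and is not a sign of failed robustness. The models for the secondary end points should likewise have their covariates named in advance.

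The cost is wording only. The sample size does not change, and the variables are already scheduled for collection. The downsides are that the team must commit to a list early and must state how missing baseline values are handled. The Overview says data from the first 375 patients are already used to train prediction models, so the list should be fixed and dated before any comparison of outcomes by arm.

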### Instruments and Measures

All recruited patients will receive additional supportive care in conjunction with standard care. Patients in the standard practice group and those in the enhanced behavioral and psychological monitoring group of the study will receive wearable devices and complete an initial evaluation on the CARDIOCARE mobile app.

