Moreover, previous research has highlighted considerably higher mortality rates among patients with breast cancer of a low socioeconomic status (ie, education, employment, and income) compared to those whose socioeconomic status is higher [34,35]. This is a critical datum as socioeconomic disadvantage may result in later-stage diagnosis and poorer access to and quality of care. Using technologically advanced tools—provided to patients by the clinical centers—able to consistently monitor several health parameters beyond the time the patient stays at the clinical center, the CARDIOCARE health care model attempts to address the economic and societal challenges that afflict both our health care system finances and patients of a lower socioeconomic status. In addition, once the prospective study is concluded and the data are analyzed, a cost-effectiveness analysis will be conducted comparing the CARDIOCARE health care model to current practices.

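### The cost-effectiveness ratio is described as the CARDIOCARE model against current care, but neither trial arm represents current care

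*Protocol article*

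**What the plan says.** **The economic comparison.** Under Statistical Considerations Regarding the Design, "the health and QoL outcomes observed during the study will be used to calculate the QALYs". These are combined with cost data to give the "cost per QALYs associated with the implementation of the CARDIOCARE model and the eHealtHeart interventions". The incremental ratio is then meant to evaluate the model's "effectiveness compared to current care practices" and to inform the allocation of health care resources. The Discussion, under Expected Findings, says that after the study "a cost-effectiveness analysis will be conducted comparing the CARDIOCARE health care model to current practices".

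**The arms.** Study Design states: "Patients in both arms, in addition to standard oncological care, will receive eHealth monitoring", by means of the watch and the chest strap. Patients in both arms also "will have access to the ePsycHeart assessment tool on the CARDIOCARE mobile app" and are given a smartphone carrying the app. Only the eHealtHeart interventions are reserved for the intervention arm. Instruments and Measures adds: "All recruited patients will receive additional supportive care in conjunction with standard care". Study Time Points and Procedures applies one schedule of procedures to both groups.

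**The concern.** The control arm is called standard practice, but it receives a monitoring package that standard practice does not include. The article itself treats monitoring as an active part of the model. In the Introduction, ePsycHeart informs patients and physicians through recommendations. In the Discussion, benefit is attributed to alerts and to the fuller information that clinicians obtain from the devices and app.

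If the ratio is computed from the two arms and reported as the model against current care, it answers a different question from the one stated. A payer moving from current care to the model would take on the monitoring as well as the eHealtHeart modules. The randomised contrast says nothing about what the monitoring part adds in cost or in health. A statement on resource allocation built on that ratio would rest on the wrong comparison.

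**Working it through.** The plan gives no figure for the economic analysis, so there is none to reproduce. The check sets the arms beside the stated comparison.

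**Inputs**
- S: standard oncological care, both arms (Study Design).
- M: shared components, both arms: wearables, smartphone, ePsycHeart (Study Design), extra supportive care (Instruments and Measures) and common procedures (Study Time Points and Procedures).
- E: eHealtHeart content reserved for the intervention arm (Study Design; The CARDIOCARE Mobile App).

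**Step 1: what the arms identify.** Write C(.) for mean cost and Q(.) for mean QALYs.
- Intervention arm: S + M + E. Control arm: S + M.
- Cost difference: ΔC_E = C(S+M+E) − C(S+M).
- QALY difference: ΔQ_E = Q(S+M+E) − Q(S+M).
- Within-trial ratio: ΔC_E / ΔQ_E.

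**Step 2: what the text claims.** The model against current care is S + M + E against S. With ΔC_M = C(S+M) − C(S) and ΔQ_M = Q(S+M) − Q(S), that ratio is

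(ΔC_E + ΔC_M) / (ΔQ_E + ΔQ_M).

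**Step 3: the gap.** Neither ΔC_M nor ΔQ_M can be obtained from the two arms, because no patient is followed under S alone. A larger sample would not help.

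**Step 4: direction.** If both QALY increments are positive, the claimed ratio lies between ΔC_E/ΔQ_E and ΔC_M/ΔQ_M. The within-trial ratio could therefore be more or less favourable than the claimed one. In the special case where monitoring has no QALY effect, the two differ by ΔC_M/ΔQ_E. The documents give neither term.

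**Step 5: is there another source for S?** None is described for this analysis. The retrospective data from 5 centers (Novelty and Study Aim) are stated only for the risk prediction model.

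**Step 6: what exactly is E?** The article is not consistent here.
- Study Design reserves the eHealtHeart interventions for the intervention arm.
- Novelty and Study Aim, with Table 1, counts physical activity, pelvic floor exercises and fall prevention as eHealtHeart.
- The CARDIOCARE Mobile App section restricts four modules: Cognitive Stimulation, Education and Training, Vision and Hearing, and Psychology and Well-being apart from its questionnaires. Mobility and Vitality and Geriatric Syndrome Assessment are not on that list, although the latter holds the incontinence and fall submodules.

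On the Mobile App wording, controls can also use some eHealtHeart content. That content would then belong in M and would cancel too.

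**The case against.** The strongest reply is that the source of the comparator is inferred. The article ties QALYs to study outcomes but does not say that the ratio is the difference between the two arms. It names the model and the eHealtHeart interventions as two things to be valued, and it places the comparison with current practice after the study ends. A health-economics plan could supply an external or modelled comparator, and an article often leaves such detail out. This stands to the extent that the final analysis may be sound. It does not remove the problem in the text: the stated comparator matches neither arm described, and no other source is mentioned.

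A reader might infer more than the documents support:
- **That device, platform and staff costs will be left out of the analysis.** This is not settled. The cost list in Objectives and Rationale does not name devices or platform, but costing the implementation of the model could include them.
- **That the shared part is the most expensive part.** No component cost is given, and the phones and wearables are returned at month 6.
- **That the ratio is off by a particular amount per QALY.** Any such figure would come entirely from assumed costs and gains.
- **That the control arm is monitoring only.** Step 6 shows that the module list does not support this label.
- **That the trial's other comparisons are undermined.** Cost-effectiveness is one of many secondary end points. The randomised estimates for the other end points do not depend on how this ratio is described.

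**Conclusion.** The concern holds as a mismatch between the stated economic comparator and the described arms. From the two arms, the trial can estimate the cost-effectiveness of the reserved eHealtHeart modules added to shared monitoring. It cannot estimate the cost-effectiveness of the whole model against current care.

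This rests on the arms being as Study Design and Instruments and Measures describe them, and on the article naming no external comparator. The size and direction of the error cannot be given from the documents. The within-trial economic analysis remains valid for the narrower question. The point should be corrected before analysis because it changes what the ratio may be said to show.

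**What to change.** 1. In Statistical Considerations Regarding the Design and in Expected Findings, define the within-trial ratio as intervention arm versus control arm: the eHealtHeart modules reserved for the intervention arm, added to the monitoring that both arms share. Remove the claim against current care from that ratio.
2. Before labelling the contrast, reconcile The CARDIOCARE Mobile App section with Study Design, Novelty and Study Aim, and Table 1 on which modules controls can use.
3. If a comparison with current care is wanted, report it separately as a non-randomised, model-based scenario. Name the source of current-care costs and QALYs, include device and platform costs, and vary the assumed benefit of monitoring instead of fixing it at one value.

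Items 1 and 2 cost wording and one clarification. Item 3 costs one further analysis and a data source. Nothing changes in conduct, randomisation or sample size, and the arms need not be renamed, which matters with 375 of 750 patients already recruited. The downside is a narrower economic conclusion from the trial itself.
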